## Abstract

**Background:**

Exposures to endocrine disrupting chemicals (EDCs) have been linked to chronic diseases including breast cancer, metabolic syndrome, diabetes, and infertility. Exposure during pregnancy may have a lifelong impact on the fetus. Services are needed to allow individuals to learn about their personal EDC exposures and how to reduce them. Million Marker (MM) aims to crowdsource and scale the biomonitoring of environmental chemicals and provide actionable results to empower individuals to proactively assess, track, and reduce their EDC exposures. In previous research, we developed and tested the first mobile EDC intervention service (mail-in urine testing and exposure report-back) for its efficacy in increasing EH literacy (EHL), willingness to reduce exposures (i.e., readiness to change, RtC), and system usability. After intervention, we found increased EHL, increased RtC in women (but not men), and decreased EDC exposure. However, some participants did not increase their RtC and had difficulty carrying out the intervention on their own. The reasons for these less optimal results were the difficulty in the EHL subject matter—participants still felt ill-prepared to apply their knowledge to making healthier lifestyle changes. Therefore, in this study, we will address these perceived limitations.

**Methods:**

We will test a self-directed online interactive curriculum with live counseling sessions and individualized support modeled after the highly effective Diabetes Prevention Program (DPP). Recruiting from the Healthy Nevada Project (HNP), one of the largest population health cohorts in the world, we test the effectiveness of our EDC-specific online intervention curriculum via EHL and RtC surveys and determine changes in EDC exposure before and after intervention in a randomized controlled trial. We will also test for common clinical biomarkers via a commercially available at-home test (Siphox). We will recruit and randomize 300 women and 300 men of reproductive age (total *n*=600) from HNP. Our target population is men and women of reproductive age (18–44 years old).

**Discussion:**

At the conclusion of this project, we will be well-positioned to scale our services to clinics and the general public, with the eventual aims of FDA approval, insurance coverage, and incorporation into routine clinical care.

**Supplementary Information:**

The online version contains supplementary material available at 10.1186/s13063-024-08627-3.

## Background

### The exposome, endocrine-disrupting chemicals, and health

The exposome encompasses the totality of environmental exposures across one’s lifespan [1, 2]. It includes exposures from the food and water, air and household and personal products, as well as social capital, stress, and other contextual elements [3]. The exposome works in tandem with the genome to determine our health and physiological state [1]. Many everyday products contain endocrine-disrupting chemicals (EDCs), which can alter the normal endocrine function of biological systems. Due to their ubiquitousness, impacts on the environment, wildlife, and human health, EDCs have become a major public health concern [4]. Data from the National Health and Nutrition Examination Survey (NHANES) has shown that more than 90% of US adults have detectable levels of common EDCs, such as bisphenol A (BPA) and phthalates, in their urine [5, 6]. Exposures to EDCs have been linked to chronic diseases in both men and women, including breast cancer, [7, 8] obesity, [9–11] metabolic syndrome, [12] diabetes, [13] and infertility [14, 15]. EDC exposures are particularly concerning for reproductive-aged women. Women are the primary consumers of many personal care products, [6] and exposures during pregnancy predispose the fetus to adverse health effects later in life, [16] including cancers, IQ loss, neurotoxicity, attention-deficit hyperactivity disorder, childhood obesity, adult obesity, Type 2 diabetes, cardiovascular and metabolic disease, genital defects, infertility, pregnancy complications, and mortality from reduced testosterone [4, 7, 9–11, 16–24].

### Need for EDC intervention

Endocrine-disrupting chemicals (EDCs), including bisphenols, phthalates, parabens, and oxybenzone, are present in over 90% of the population at any one time, [5, 6] and have been linked with numerous health effects in laboratory and human studies, including breast cancer, [7, 8] obesity, [9–11] metabolic syndrome, [12] diabetes, [13] and infertility, [14, 15] and effects on the fetus that can manifest later in life, including cancers, IQ loss, neurotoxicity, attention-deficit hyperactivity disorder, childhood obesity, adult obesity, type 2 diabetes, cardiovascular and metabolic disease, genital defects, infertility, pregnancy complications, and mortality from reduced testosterone [4, 7, 9–11, 16–25].

BPA is used to make polycarbonate plastic and epoxy resins and is found in numerous consumer products (e.g. thermal receipts, plastic foodware, can linings). BPA is a known hormone disruptor and has been linked to numerous health effects in laboratory animals [23] and chronic diseases and disorders in humans, including infertility, cardiovascular and metabolic disease, asthma, and child development [16]. It has also been deemed a mammary carcinogen [24]. Due to these health concerns, BPA has been increasingly replaced with other bisphenols (BPs), which are structurally or functionally similar to BPA, (such as BPS and BPF) and share many of the same health concerns as BPA [26–29]. Phthalates are used as to make plastic flexible and are added to fragrances to disperse scent [30]. Phthalates are also hormone disruptors; they have long been known for antiandrogenic effects (i.e. decreased anogenital distance in infant boys) [31–33]. Phthalate exposure is also associated with infertility, type 2 diabetes, asthma, and other health problems [34]. Parabens are a group of chemicals widely used as antimicrobial preservatives in personal care products and packaged food. Parabens are hormone disruptors, showing estrogenic and antiandrogenic activity, as well as blocking aromatase. Exposure has been linked to adrenal and thyroid disruption, metabolic changes, developmental-behavioral changes in animals, [35] and reduced fertility in humans [36]. Oxybenzone is a UV filter that is found in many sunscreens, hair products, cosmetics, and lotions [37, 38]. Oxybenzone is an EDC—it has been shown to be proliferative in estrogen-responsive cancer cell assays, [38, 39] as well as promoting the growth of androgen-dependent prostate cancer cells [40].

These EDCs have relatively short half-lives in the body (i.e. 6 hours to 3 days) [41–43]. Therefore, the fact that most of the population is exposed at any one time [5, 6] indicates ubiquitous and constant exposure sources. However, the rapid elimination from the body also allows for reduction of internal exposure with removal or avoidance of the exposure sources from daily life. Thus, interventions aimed at identifying exposures (through internal and external assessments) and removing them (via personalized recommendations based on exposure levels and lifestyle habits), have the potential to greatly reduce transient EDC exposures, as demonstrated in our previous work [44].

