## Intervention

### The Millon Marker (MM) test kit and report-back

The MM EDC testing panel consists of 13 metabolites, assessing exposure to EDCs that are commonly found in household and personal products. These chemicals are found in over 90% of the US population (at any one time) [5, 15, 21, 22, 62].

Consented participants will be mailed the MM *Detect and Detox* kit. Upon receipt, participants in the intervention group will 1) engage in a Zoom call with a MM coach to complete a comprehensive 24-hour food/product Lifestyle Audit the day before their urine sample collection, 2) collect first void urine sample the next morning, 3) send back samples via FedEx, 4) receive results as well as personalized recommendations for products and lifestyle changes to reduce EDC exposures, 5) follow the recommendations and make changes to reduce exposures, 7) test again after 3 months. Participants in the control group will complete Steps 2-7, and will receive a report-back with more generalized recommendations. Participants will be guided through this journey from our online instructions, online video tutorials, extensive educational materials, and email communication.

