### The endocrine-disrupting chemical (EDC) environmental health literacy (EHL) curriculum

Our 8-week education curriculum and intervention program is modeled after the Diabetes Prevention Program (DPP) [52] and Omada Health (digital DPP) [63] with the goals of building EDC-related behavioral knowledge and skills for sustained behavior change to minimize exposures. This intervention is intended to help users to 1) better understand their MM Test Kit Exposure Report results, 2) learn about various sources of toxic chemical exposures, 3) learn ways to reduce EDC exposures in various environments, 4) learn how to build behavioral skills to implement and maintain lifestyle changes practically, and 5) feel a sense of community, accomplishment, and accountability. The curriculum is self-directed, with participants required to complete at least 6 of the 8 classes within an 8-week period. See Table 1 for the course overview.

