### Surveys, study measurements and secondary outcomes

EDC levels will be measured at baseline and 3 months. Participants' age, level of education, income, BMI, self-assessed health status, smoking status, alcohol intake, exposure to other toxic substances (e.g. dangerous chemicals, radiation), will be collected via questionnaires after recruitment to the study. We will measure participants’ environmental health literacy (EHL), readiness to change (i.e. readiness to reduce exposures, RtC), and well-being (general health, social support, financial well-being, sleep, stress, and physical activity) at baseline, 3 months (post-intervention surveys), and 6 months (exit surveys) after baseline (see Fig. 1). We will also assess usability and participant satisfaction 3 months after baseline (post-intervention). The EHL survey was adapted from the framework of the “general environmental health scale” section of the survey by Lichtveld et al. [66] which was validated in two geographic areas via exploratory and confirmatory factor analysis. Questions include those regarding individuals’ environmental health knowledge (e.g. “Household dust contains harmful chemicals”), attitudes (e.g. “I am concerned about chemicals I am exposed to through products I buy”), and behaviors (e.g. “I take steps to avoid inhaling cleaning products”). We adapted the RtC survey based on the Transtheoretical Model of Health Behavior Change [67] in which we ask about current efforts and interest in limiting exposure to harmful chemicals. EHL and RtC will be assessed to determine their association with EDC levels, as well as the effect of the intervention on EHL and RtC.

We will also measure participants’ well-being via relevant questions from three validated surveys. General health and sleep will be assessed using questions from the Behavioral Risk Factor Surveillance System; [68] stress will be measured via the Perceived Stress Scale (PSS), [69] and physical activity will be assessed using the International Physical Activity Questionnaire [70, 71]. These secondary health outcomes will be measured at baseline, 3-month and 6-months later to assess changes.

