### Data collection, management, and analysis

The MM *Detect and Detox* kit is an at-home sample collection service that participants will use to collect their own samples. The mailed kit has the following components: kit box, instruction card with activation code, sterile urine collection cup, biohazard bag with absorbent paper, pre-labeled polymailer. We have built a secure online portal for users to make accounts, register their kits, track the status of their samples, and view their testing results and feedback online. For the Lifestyle Audit, participants in the intervention group will schedule a Zoom call with a MM lifestyle coach to document the food, drinks they consumed, as well as all the products (personal care and household products) they used on the day prior to urine collection. MM’s technology team will oversee the security of MM’s software stack and servers, ensure that the platform is HIPAA-compliant, and oversee the software building and maintenance for this project.

Several emails will be sent to the participants to update them on their sample and report statuses and keep them engaged. FedEx Priority Overnight shipping will be used to ensure the sample quality. The turnaround time for the lab analysis and MM report generation is 2-4 weeks. Three months after submitting their baseline urine sample, participants will be sent the second kit and go through the same process again and submit their second samples. Detailed flow of events is illustrated in Fig. 1.

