A third party, internationally well-known state-of-the-art laboratory is in contract with MM to perform the sample analysis. The lab staff will be blinded to participants’ identifiable information to ensure no bias will be introduced during sample analysis. The following common EDCs [75] are included in the panel: bisphenol A (BPA), detected in 95% of NHANES participants; [5] bisphenol S (BPS) and bisphenol F (BPF), detected in 89% of NHANES participants; [21]; low molecular weight phthalates, including mono-ethyl phthalate (MEP) and mono-n-butyl phthalate (MBP), metabolites of diethyl phthalate (DEP) and dibutyl phthalate (DBP); high molecular weight phthalates, including, mono(1-ethylhexyl) phthalate (MEHP), mono(2-ethyl-5-carboxypentyl) phthalate (MECPP) and mono(2-ethyl-5-hydroxyhexyl) phthalate (MEHHP) metabolites of di-(2-ethylhexyl) phthalate (DEHP) detected in over 90% of NHANES participants; [22] methyl paraben, ethyl paraben, propyl paraben, and butyl paraben, found in 90% of NHANES participants, [76] and benzophenone-3 (BzP-3), detected in 97% of NHANES participants [62].

We will analyze urine samples by Liquid Chromatography Mass Spectrometry (LCMS) for the presence of the target metabolites listed above. All targets have commercially available isotopically labeled standards, called “surrogates.” The isotopically labeled surrogates will be spiked into the urine before sample preparation. The level of the surrogates will be determined during method verification. Sample preparation will consist of solid phase extraction per the protocol established during method verification. A solvent blank will be prepared concurrently. An internal standard will be spiked into each sample and blank after extraction. Native target response, if detected, will be reported as a ratio to the isotopically labeled surrogate. Two replicates will be run per sample to ensure reproducibility and repeatability as part of the quality control and assurance. Results will be reported to MM including sample ID, date received, date analyzed, metabolite levels, limit of quantification and detection, as well as specific gravity (to adjust for individual hydration status).

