For the analysis plan, we will examine the distribution and concentrations of each of 13 chemical analytes in urine to determine geometric means, medians, percentiles and ranges of exposures. We will compare the percentiles with those reported in the NHANES study. We will include BMI, age, gender, diet, education and household income as covariates. Participants’ dietary patterns will be captured prior to sample collection by looking at their consumption of packaged food and times eating out as these are important culprits of EDC exposures. We will conduct an intent-to-treat analysis. The primary outcomes are the pre-post (first and second tests) differences in specific gravity-adjusted concentration levels per analyte. Clinical biomarkers measured before and after the intervention will also be compared to assess improvement in health and reduced disease risk. We willassess changes in participants’ EHL, RtC and well-being before and after the interventions as well. We will first generate summary statistics on participants’ responses. Changes will be calculated based on paired values of individual responses.

For all analyses, data will be reviewed to ensure assumptions are not violated. If outcomes are not sufficiently normally distributed for parametric tests to be valid, nonparametric tests will be conducted. If needed, variables with response categories with too few participants will be combined. Attrition analyses will be run to compare demographic variables between participants who completed post-test surveys and those who did not.

Summary data and associations between demographic variables and EHL, RtC, well being, EDC metabolites, and clinical biomarkers will be analyzed for all participants with pre-test survey data. Independent sample t-tests, one-way ANOVAs, Chi-square tests, and Spearman’s rank correlations will be run as appropriate. Changes from pre-test to post-test comparing differences between the intervention and control groups, will be analyzed for participants who completed both surveys using regression analyses, controlling for significant demographic variables.

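### One first-void urine per test leaves day-to-day variation in the primary outcome unmeasured, and the steps just before sampling differ between arms

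*Protocol article*

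**What the plan says.** The Background (Need for EDC intervention) says: "These EDCs have relatively short half-lives in the body (i.e. 6 hours to 3 days". The same paragraph argues that widespread detection "indicates ubiquitous and constant exposure sources".

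The outcome is defined in Data collection, management, and analysis: "The primary outcomes are the pre-post (first and second tests) differences in specific gravity-adjusted concentration levels per analyte". The timing is in Surveys, study measurements and secondary outcomes: "EDC levels will be measured at baseline and 3 months".

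The test kit section has participants "collect first void urine sample the next morning", and the kit contents in the data collection section list one urine cup. The kit is an "at-home sample collection service that participants will use to collect their own samples". The only replication is in the laboratory: "Two replicates will be run per sample to ensure reproducibility and repeatability".

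The arms differ just before sampling. Intervention participants book a video call with a coach to audit food and product use on the day before the void. Controls start at the next step, the void itself. Kits go out after randomization (Intervention design), so this applies to the baseline sample too, and the second kit repeats the process. The curriculum aims at "sustained behavior change to minimize exposures".

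**The concern.** There are two separate issues.

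The first is precision. With half-lives of hours to a few days, one void reflects recent exposure. Within-person variation enters both the baseline and the 3-month value, and so enters the difference twice. Laboratory replicates reduce assay error only. Specific gravity corrects for hydration only.

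The second is comparability. A short half-life means that a careful day or two can lower a value. In one arm the void follows a call, at a time the participant chose, whose subject is that day's exposures. By the second test this arm has also had the curriculum and coaching. Randomization balances people. It does not balance a measurement procedure that differs by arm. At stake is whether an arm difference reflects usual exposure or behaviour around the test.

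**Working it through.** **The plan's own figure.** Sample size gives 300 per arm less 50% attrition: 300 × 0.5 = 150, which reproduces. The article gives no effect size, SD, alpha or power for the urine outcome, so its power statement cannot be recomputed.

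**Precision.** Assumptions, none from the document: log scale, one-sample SD set to 1, ICC 0.2 to 0.8, no variation between people in true change, independent day-to-day deviations, 80% power, two-sided 0.05. From the document: 150 per arm and change from first to second test.

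- Variance of change with m voids per test = 2(1 − ICC)/m.
- Detectable difference = (1.96 + 0.84) × SD of change × √(2/150).

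| ICC | SD of change, 1 void | Detectable, 1 void | SD of change, 2 voids | Detectable, 2 voids |
|---|---|---|---|---|
| 0.2 | 1.265 | 0.409 | 0.894 | 0.289 |
| 0.4 | 1.095 | 0.354 | 0.775 | 0.251 |
| 0.6 | 0.894 | 0.289 | 0.632 | 0.205 |
| 0.8 | 0.632 | 0.205 | 0.447 | 0.145 |

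If the analysis adjusts for baseline instead, the figures are 0.317 against 0.236 at ICC 0.2, and 0.194 against 0.141 at ICC 0.8.

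**When days are not independent.** In a one-compartment model with a 3-day half-life, deviations 2 and 3 days apart correlate at 2^(−48/72) = 0.63 and 2^(−72/72) = 0.50. Averaging two voids multiplies within-person variance by (1 + r)/2, giving 0.815 and 0.75, a cut of 18.5% to 25% and not 50%. At ICC 0.4 the detectable difference falls from 0.354 to 0.354 × √0.815 = 0.320 or 0.354 × √0.75 = 0.307.

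**What the laboratory duplicate buys.** Suppose assay error is 2%, 5% or 10% of total variance, within a within-person share of 0.6 (ICC 0.4). The second run removes half of it: 0.01/0.6 = 1.7%, 0.025/0.6 = 4.2%, 0.05/0.6 = 8.3% of the variance of change.

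**Is the individual change mostly noise?** Noise share = 2(1 − ICC)/[2(1 − ICC) + f × ICC], where f is the variance of true change relative to between-person variance. For f from 1 down to 0.25, the share is 89% to 97% at ICC 0.2, and 33% to 67% at ICC 0.8. The answer depends on a figure the document does not give.

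**Avoidance.** Fraction left after 24 hours without exposure = 2^(−24/half-life): 2^(−4) = 6% at 6 hours and 2^(−1/3) = 79% at 3 days. These are limits for complete avoidance; partial avoidance does less.

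**Direction.** Lower values at baseline in the intervention arm would shrink its measured fall. Lower values at the second test would enlarge it. Equal effects at both tests would largely cancel on the log scale. Effects need not be equal, because training comes in between. The document does not settle the sign.

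**The case against.** Steady daily intake gives stable levels at any half-life, and the protocol argues that sources are constant. That is fair as a limit on what half-lives alone can prove. However, the argument rests on how many people test positive, not on repeat measurements within a person.

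The power statement cites the sponsor's previous work, which used the same mail-in test. Standardized effects from that work would already contain day-to-day variation. It also found a fall in monobutyl phthalate in 55 retested participants (p<0.001). This stands as evidence that noise need not swamp change, although it is one analyte without a control group.

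Controls are advised too: their report gives general recommendations on diet, home and products, so the difference in training is one of degree. Dietary patterns before sampling are recorded and used as a covariate. Both points soften the comparability concern. Neither removes the audit that only one arm has.

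That participants choose the collection day is an inference. It is well grounded for the intervention arm, where they book the call. For controls it rests on home collection with no stated day. The article fixes the second test at about 3 months and mentions a standard sampling procedure, and the full protocol may set a window. The absence of a window in the article is therefore not the finding; the arm-specific step is.

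A reader might infer that the pre-post change is mostly noise, that the trial is underpowered, or that a positive result would be worthless. The document supports none of these. It gives no within-person variance, the loss shown is relative to an alternative design, and differential avoidance is plausible but not demonstrated.

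**Conclusion.** The concern holds in two limited parts.

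First, one void per test leaves day-to-day variation unmeasured, and the planned replication does not address it. Under the stated assumptions, a second independent void would lower the detectable difference by a factor of 1/√2 at any ICC. For the longest half-lives the gain is much smaller. Noise that is equal in both arms does not bias the comparison of mean change.

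Second, the sampling conditions differ by arm at both tests. This does not depend on the ICC, and larger numbers would not cure it. Its size and direction are unknown. It means that a positive result could not be cleanly attributed to a change in usual exposure. It is worth correcting because the correction is nearly free.

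**What to change.** **1. Same sampling conditions in both arms.** In the test kit and data collection sections, state one rule: an assigned collection morning in a short window after kit receipt, the same type of weekday at both tests, and an instruction to keep the current routine. Align what happens before the void, for example by holding the audit call after collection, or by giving controls an equally timed record of the previous day without coaching. Cost: a portal setting, a line in the instructions and some rescheduling of calls. An announced morning still allows test-day avoidance, so this limits the problem and does not remove it.

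**2. Two first voids per test, where storage stability allows.** Collect them a few days apart. Pool them, or spend the two planned runs on the two voids. Start at a wave boundary so that each participant has the same scheme at both tests, since enrolment is already under way. Costs: a second cup and collection when 50% attrition is already planned for; short home storage, set against the overnight shipping meant to protect quality; fewer technical duplicates if not pooled; an audit covering only one of the days; and weaker comparability with single-void reference values and earlier waves.

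If the second change is not adopted, the sponsor should justify a single void with a within-person variance figure, for example from repeat samples of existing users if it holds them.
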